#### Participant timeline {13}

Eligible participants who are referred to our hospital will be recruited. Participants will be asked to complete an informed consent form by an on-site researcher if they choose to participate in the study (Fig. 1). They will complete the baseline assessments and will be randomly assigned to the intervention or control group. All patients will have follow-up visits monthly, and all outcome data will be collected by research assistants (Table 1).

**Table 1 Tab1:**
[figure not shown]
Overview of the study period (SPIRIT Fig. 2013). PS performance status, MRI magnetic resonance imaging, and BMD bone mineral density

Participants will be checked for adverse effect existence, vital sign calculation, physical measurements, and performance status evaluation every visit. Questionnaires, laboratory tests, and imaging (ultrasound, MRI, and BMD) will be conducted before, 8 weeks, and after the start of the relugolix administration

ECOG-*PS* Eastern Cooperative Oncology Group Performance Status, *MRI* magnetic resonance imaging, *BMD* bone mineral density

#### Sample size {14}

Considering the results of leiomyoma volume reduction rate after the 12 weeks of continuous administration of 20 mg and 40 mg relugolix [19], we assume a change from baseline as − 41% and − 36% for the daily and every other day groups, respectively, and a common standard deviation (SD) as 30%. Set the non-inferiority margin as 20%, the significance level as 2.5% (one-sided), and the power as 0.8; the sample size requires a minimum of 64 patients in each group. Considering a dropout rate of approximately 10%, the total number of patients in this trial will be set at 70 patients in each group, for a total of 140 patients.

#### Recruitment {15}

Post the information on the website and disseminate it to related facilities.

### Assignment of interventions: allocation

#### Sequence generation {16a}

A minimization adaptive randomization will be used for random assignment, using (1) the number of leiomyomas (2 or less or 3 or more), (2) maximum tumor diameter (5 cm or more or less), and (3) age (45 years or more or less) as adjustment factors so that there is no large bias and ensuring equal recruitment of intervention and control participants. Because the number of adjustment factors is large compared with the sample size, and a stratified permuted block randomization might not perform well, we select a minimization adaptive randomization. To reduce the risk of bias, attending physicians as researchers who will be part of the intervention will fill out all outcome data into the case report form (CRF), and data analysts will be blinded to group allocation. Eventually, this study will be no blinding, and group changes will not be allowed after the randomization.

#### Concealment mechanism {16b}

Trained research assistants will facilitate the collection of questionnaire data, physical measurements, vital signs and occurrence of adverse events, imaging assessment data, BMD, and blood tests. Imaging data includes an ultrasound examination which will be performed by the attending physician and MRI which will be outsourced and reported by its radiologist. A trained clinical laboratory technician experienced with blood collection will collect small blood samples from the patients and then analyze them immediately. Inspection items that cannot be analyzed at our hospital will be outsourced.

#### Implementation {16c}

Randomization will be conducted at the registration of patients’ data after informed consent completion. We use INDICE (UMIN Internet Data and Information system for Clinical and Epidemiological research) cloud for randomization, and initial settings will be made by the responsible allocator completely separated from the study. The INDICE is a system provided by the University Hospital Medical Information Network (UMIN) that is used for patient registration in clinical trials in Japan. It operates on the Internet to create a network-based medical research infrastructure by establishing a coordinating center on the network to support the execution of investigator-initiated medical research. Then, it is acceptable that once the initial settings are made by the person responsible for the allocation, the randomization is automatically made by entering the information during case registration by the principal investigator or collaborator.

### Assignment of interventions: blinding

#### Who will be blinded {17a}

This is an open-label trial.

#### Procedure for unblinding if needed {17b}

Not applicable.

### Data collection and management

#### Plans for assessment and collection of outcomes {18a}

Eligible participants will be invited to complete questionnaires, physical measurements, vital signs, imaging, laboratory, and bone mineral density testing as a baseline before randomization. The regular items of vital signs, body weight, PS, and the existence of adverse effects will be verified monthly after the beginning of the study. Before the administration, 8 weeks, and after 24 weeks of relugolix administration, laboratory tests, ultrasound examinations, and questionnaires will be conducted in addition to the monthly regular items. Additional examinations including laboratory tests or ultrasound examinations will be conducted in case the attending physician determined it necessary. Questionnaires include the number of days with abnormal genital bleeding and the Kupperman Index. Kupperman Index covers 11 menopausal symptoms including hot flushes (vasomotor), paresthesia, insomnia, nervousness, melancholia, vertigo, weakness, arthralgia or myalgia, headache, palpitations, and formication. Each symptom is rated on a scale from 0 to 3 for having no, slight, moderate, or severe complaints, respectively, with the highest possible total score being 51. Imaging will be admitted by magnetic resonance imaging (MRI) examination, by which select the leiomyoma with the longest diameter (excluding a calcified leiomyoma), measure in three directions in a metric system (vertical and horizontal lengths by coronal section and anteroposterior diameter by sagittal section), and calculate the volume (D1 × D2 × D3 × *π*/6) from the 3 diameters (D1, D2, and D3). Pelvic MRI scans just after the completion of the relugolix administration are acceptable with a timing error of ± 1 week. For abnormal genital bleeding, the total number of days of bleeding will be recorded using a patient diary.

#### Plans to promote participant retention and complete follow-up {18b}

Patients visit our hospital monthly, and each attending physician fills out the CRF. Revealed with severe adverse effects related to the administration of relugolix, the attending physician will examine and consult a specialist, and the principal investigator will decide whether to discontinue the trial or not, taking the participant’s wishes into consideration. The administrator of the institution will be notified, and the case will be reported to an accredited clinical research review committee. Compensation insurance will be purchased to compensate for any health problems that may occur to research subjects in relation to the clinical research. In preparation for liability, the principal investigator will purchase liability insurance.

#### Data management {19}

The data management will be conducted as follows: (1) After obtaining written consent, the principal investigator/participating physician checks eligibility and completes the CRF. (2) The principal investigator/participating physician checks for omissions on the CRF, enters the medical record number and subject ID on a collation sheet, and brings the CRF to the data center. At the data center, the principal investigator/participating physician reconfirms eligibility and performs the allocation process using the INDICE cloud. (3) After the allocation process is completed, the principal investigator/participating physician enters the allocated groups in the CRF and the collation sheet. (4) In case of withdrawal of consent, discontinuation, dropout, etc., the data center will be notified immediately.

#### Confidentiality {27}

The personal information in this study will be stored on unnetworked PCs in the medical office and laboratory or in a locked archive. The collation sheet will be managed by the personal information manager. [name] as the principal investigator will be appointed as the personal information manager.

#### Plans for collection, laboratory evaluation, and storage of biological specimens for genetic or molecular analysis in this trial/future use {33}

Once blood tests have been completed, any leftover samples will be transported to the obstetrics and gynecology laboratory at Nara Medical University for biobanking and future research. Samples will be used when only approved by the Research Ethics Board. Samples will be labeled with a study identification number prior to storage. The linkage document to collate patient and identification number will be stored in a vault. The principal investigator shall preserve documents related to the conduct of the study (e.g., notification documents from the hospital director, copies of various application forms and reports, research subject identification code lists, informed consent forms, case report forms, etc., and other documents or records necessary to ensure the reliability of the data) and destroy them in anonymized form 5 years after the research is published.

## Statistical methods

### Statistical methods for primary and secondary outcomes {20a}

The assessment of primary endpoint will be assessed as follows: we defined the null hypothesis as “The mean rate of change in the intervention group is more than 20% inferior to the mean rate of change in the control group,” and this will be tested with a one-sided *t*-test at a significance level of 2.5%. In addition, 95% confidence intervals for the mean rate of change are calculated for each group and for the difference between the groups. The assessment of the secondary endpoint will be analyzed as follows. (1) Change in uterine volume from before study drug administration at 24 weeks after study drug administration (%). The measured values before the start of treatment and at 24 weeks and the rate of change at 24 weeks will be summarized for each group using descriptive statistics. The 95% confidence interval of the difference between the groups will be calculated for the mean of the rate of change. (2) Change in the total score of the Kupperman Index from before the study drug administration at 24 weeks after the study drug administration (points). (3) Percent change in bone mineral density (BMD) from baseline at 24 weeks post-treatment (%). The measurements before and at week 24 of treatment and the percent change at week 24 of treatment will be summarized for each group by descriptive statistics. In addition, the null hypothesis “the mean rate of change for the intervention group is equal to the mean rate of change for the control group” will be tested with a two-sided 5% *t*-test at the significance level. In addition, 95% confidence intervals for the mean rate of change will be calculated for each group and for the difference between the groups. (4) Percentage change in bone metabolism markers (serum BAP) at 24 weeks after treatment compared to before treatment with the study drug (%). The measured values before the treatment and at 8 and 24 weeks of treatment, and the change (%) at 8 and 24 weeks of treatment will be summarized for each group using descriptive statistics, and a graph of the mean ± standard deviation will be prepared for each time point. The null hypothesis “the mean of the amount (rate) of change in the intervention group is equal to the mean of the amount (rate) of change in the control group” is tested with a two-tailed *t*-test at a significance level of 5%. In addition, 95% confidence intervals for the mean of the amount (rate) of change will be calculated for each group and for the difference between the groups. Data for each endpoint will be analyzed after the period for collecting the data has ended and the data have been fixed. The intermediate analysis will not be performed.

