### Trial design {8}

This is a phase IV study designed as a randomized, parallel-group comparative trial, with a 1:1 allocation for non-inferiority assessment.

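### The primary t-test ignores the three minimisation factors, so to the extent that they predict percent volume change the test is conservative and the interval wider than it need be

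*Protocol article*

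**What the plan says.** Sequence generation {16a} sets the allocation method: "A minimization adaptive randomization will be used for random assignment". The factors are "the number of leiomyomas (2 or less or 3 or more") and "maximum tumor diameter (5 cm or more or less), and (3) age (45 years or more or less) as adjustment factors". The stated purpose is to use them "as adjustment factors so that there is no large bias and ensuring equal recruitment of intervention and control participants". Trial design {8} gives the ratio, "with a 1:1 allocation for non-inferiority assessment".

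Statistical methods {20a} fixes the primary analysis. The null hypothesis is that the intervention mean is worse by more than 20%, "and this will be tested with a one-sided *t*-test at a significance level of 2.5" percent. For estimation, "95% confidence intervals for the mean rate of change are calculated for each group and for the difference between the groups". BMD and BAP each get a two-sided 5% t-test. Uterine volume gets descriptive statistics and an interval, with no test. The Kupperman score is listed just before BMD, and it is not clear whether the test described there is meant for it as well. No covariate is named for any analysis.

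Sample size {14} is built on the same unadjusted comparison: "Set the non-inferiority margin as 20%, the significance level as 2.5% (one-sided), and the power as 0.8".

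**The concern.** Minimisation makes the arms more alike on the chosen factors than simple randomisation would. If a factor predicts the outcome, this reduces the true sampling variance of the difference in means. The two-sample t-test takes no account of that. It estimates its standard error from the whole within-arm variance, including the part that the allocation has already balanced, so the standard error is overstated.

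In a non-inferiority trial the upper confidence limit for the loss of effect decides the result. An interval that is wider than necessary makes the margin harder to meet for no benefit. The information that would narrow it is already recorded before randomisation.

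**Working it through.** **Inputs.** From Sample size {14}: margin 20 (read as percentage points), assumed reductions of 41% and 36% (a true shortfall of 5), SD 30, one-sided 2.5%, power 0.80, 64 evaluable per group, 70 enrolled per group. The share of outcome variance explained by the three factors (R²) is not in the documents; 0 to 0.3 is assumed.

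**Reproducing the plan's figure.** The distance to the margin is 20 − 5 = 15. At 64 per group, SE = 30 × √(2/64) = 5.303 and the noncentrality is 15 / 5.303 = 2.83. Noncentral-t power on 126 df is 80.15%; at 63 per group it is 79.5%. The stated 64 is therefore correct for an unadjusted t-test. The 95% CI half-width is 1.979 × 5.303 = 10.50 points.

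**Adjusted model.** The residual SD is 30 × √(1 − R²), and three further degrees of freedom are used (123 left at 64 per group). For R² = 0.1 the residual SD is 28.46, SE = 28.46 × √(2/64) = 5.03, and the half-width is 1.979 × 5.03 = 9.96. The other values follow in the same way.

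**The t-test under minimisation.** With perfect balance the true SE is 5.303 × √(1 − R²), while the test still uses 5.303. Two results follow.
- One-sided error at the margin is about 1 − Φ(1.96/√(1 − R²)): 1.9%, 1.4% and 1.0% for R² = 0.1, 0.2 and 0.3.
- Power of the t-test is about Φ((15 − 10.50) / (5.303 × √(1 − R²))): 81.4%, 82.9% and 84.5%. The t-test's own power therefore rises too, and the benefit of adjustment must be measured from these values, not from 80%.

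**Simulation.** Minimisation was simulated with three balanced binary factors, a 0.8 biased coin, 64 per arm and 6,000 runs per row.

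| Assumed R² | One-sided error: t-test / adjusted | Power: t-test / adjusted | Power gain (points) | Mean half-width: t-test / adjusted |
|---|---|---|---|---|
| 0 | 2.7% / 2.6% | 79.8% / 79.7% | about 0 | 10.5 / 10.5 |
| 0.1 | 2.2% / 2.6% | 80.9% / 83.8% | 3 | 10.5 / 9.9 |
| 0.2 | 1.6% / 2.8% | 83.0% / 88.4% | 5 | 10.5 / 9.4 |
| 0.3 | 1.0% / 2.3% | 83.8% / 91.9% | 8 | 10.5 / 8.8 |

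The Monte Carlo standard error of an error rate near 2.5% is √(0.025 × 0.975 / 6000) = 0.2 points. The adjusted model's 2.3% to 2.8% is therefore compatible with 2.5%. The t-test falls progressively below it.

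A repeat at 63 per arm (70 less 10%) gave t-test errors of about 1.9%, 1.4% and 0.9%. The half-width fell from about 10.6 to 10.0, 9.5 and 8.9.

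**The case against.** The case for leaving the plan alone has real substance.

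- **The loss is conditional.** No section relates any of the three factors to percent change in volume. A reader might infer that they are known to be prognostic and that power is certainly being lost. The documents show only that they were chosen to avoid imbalance, which suggests that they were thought to matter. If R² is 0, nothing is lost.
- **The analysis is valid and consistently sized.** A reader might infer an underpowered trial or an unsafe claim. Neither follows from this point. The error is conservative, and 64 per group is right for the named test.
- **The gain is easily overstated.** Comparing adjusted power of 84%, 88% and 92% with a fixed 80% suggests gains of 4, 8 and 12 points. That comparison holds only for covariates that were not minimised, and for those the t-test is not conservative. For the minimised factors the gain is about 3, 5 and 8.
- **The SD is a separate question.** The Background cites an SD of 34.33 at 24 weeks from the phase III trial. Whether 30 was too optimistic concerns the sample size and adds no weight here.
- **Baseline is not ignored altogether.** Every endpoint concerned is a change or percent change from baseline. What is missing is baseline as a covariate. Nor is every secondary endpoint tested: the unadjusted t-test applies clearly only to BMD and BAP.
- **Covariate models are often left to the analysis plan,** which is not shown. Here, however, the protocol names the test, its sidedness and its level, and sizes the trial on it. An analysis plan that adjusted the primary test would depart from that text.

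All but the last of these limit the size and weight of the point. None removes the mismatch between allocation and analysis.

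**Conclusion.** The point stands as a recommendation on efficiency and consistency. The protocol minimises on three factors and then fixes a primary test and interval that leave them out. The direction is firm: whenever the factors explain outcome variance, the unadjusted standard error is too large.

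The size is not known. For R² of 0.1 to 0.3, with SD 30 and 63 to 64 per arm, it is about 3 to 8 points of power and roughly 0.5 to 1.7 points of half-width, with a one-sided error of about 2% down to 1% in place of 2.5%. These figures rest on additive effects of the three binary factors and count only the minimised factors; anything that log baseline volume explains beyond them would come on top. At R² of 0 the adjusted model costs about 0.1 point of power.

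**What to change.** In Statistical methods {20a}, make the primary analysis a linear model of percent change in leiomyoma volume on arm, the three minimisation factors as used for allocation, and log baseline leiomyoma volume. Test the adjusted difference against the same 20-point margin at one-sided 2.5%, and report its 95% confidence interval. Keep the unadjusted t-test as a sensitivity analysis.

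Use the same model, with each endpoint's own baseline value in place of leiomyoma volume, for the secondary between-group estimates: the uterine volume interval, Kupperman score, BMD and BAP.

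No new data are needed. The factors are required for allocation, and baseline volume is required to calculate the endpoint. Because the t-test is protocol text, the cost is an amendment to both protocol and analysis plan. Under the amendment section {25} it goes to the review board for approval, and under {20b} the change and its reason are explained in the summary report. It should be settled before the data are fixed and before outcomes are seen by arm. The sample size need not change.

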#### Intervention description {11a}

The initial dose of relugolix is 40 mg orally once daily before meals, starting on days 1–5 of the menstrual cycle until day 56. On day 57, the control group will continue taking 40 mg of relugolix every day, and the intervention group will switch to 40 mg of relugolix every other day. However, change to another group will not be permitted.

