### Outcomes {12}

The primary endpoint will be the reduction of leiomyoma volume before and after the administration of relugolix. The secondary endpoints will be the reduction (%) of uterine volume compared with pre-treatment, change (score) of total Kupperman Index score at 24 weeks compared with pre-treatment, change rate (%) of bone mineral density (BMD) at 24 weeks compared with the baseline, and change rate (%) of bone metabolism markers(serum BAP) at 24 weeks compared with the baseline. The investigative assessments will be the total number of days of genital bleeding and the change in gonadotropic and sex hormone levels such as luteinizing hormone (LH), follicle-stimulating hormone (FSH), estradiol (E2), and progesterone (P4) at 24 weeks compared with the baseline. The MRI scans will be outsourced to another hospital, and tumor and uterine volume will be evaluated by the radiologist in the hospital with blind.

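### BAP is compared by an unadjusted t-test on change from pre-treatment, which is less precise than adjusting for the pre-treatment value; the test sentence should also name percent change at week 24

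*Protocol article*

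**What the plan says.** Outcomes {12} defines the secondary endpoint as "change rate (%) of bone metabolism markers(serum BAP) at 24 weeks compared with the baseline". Item (4) of {20a} opens with the same definition: "Percentage change in bone metabolism markers (serum BAP) at 24 weeks after treatment compared to before treatment with the study drug".

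Week 8 then enters as description: "the change (%) at 8 and 24 weeks of treatment will be summarized for each group using descriptive statistics". The item also plans a plot: "a graph of the mean ± standard deviation will be prepared for each time point".

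The inferential sentence follows directly. Its null hypothesis is that "the mean of the amount (rate) of change in the intervention group is equal to the mean of the amount (rate) of change" for controls, tested by a two-sided t-test at 5%. The next sentence plans 95% confidence intervals, again on the amount (rate) of change. Neither sentence names a week or a covariate.

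Blood is taken before treatment, at 8 weeks and after 24 weeks ({18a}). Dosing is the same in both groups until day 56 ({11a}): "On day 57, the control group will continue taking 40 mg of relugolix every day, and the intervention group will switch" to every other day.

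**The concern.** There are two separate matters, and the first carries more weight.

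**Precision.** A t-test on change from pre-treatment fixes the coefficient of the pre-treatment value at 1. Unless the data happen to agree with that coefficient, the comparison carries avoidable noise. Pre-treatment BAP is a scheduled laboratory value, so using it costs nothing. BAP and bone mineral density are the only two bone endpoints among the secondary endpoints. The abstract and the closing paragraph of the Discussion look for superiority on adverse effects and on the secondary endpoints, so an interval wider than necessary weakens the evidence the trial wants.

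**Wording.** The test and interval sentences of item (4) admit two scales and come straight after a sentence listing two weeks. Item (3), on bone mineral density, summarises week 24 only and tests the rate of change only. The looser wording in item (4) should be tightened so that scale and week are fixed in the sentence that defines the test.

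**Working it through.** **Inputs from the protocol article.** Endpoint: percent change in BAP at week 24 against pre-treatment ({12} and the title of item (4)). Method: unadjusted t-test, two-sided 5% ({20a}). Samples: pre-treatment, week 8, week 24 ({18a}). Regimens diverge on day 57 ({11a}).

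**Not in the documents.** BAP standard deviations, correlations, sample size or power. The stated 64 per group is for leiomyoma volume. It reproduces (margin 20, assumed difference 5, SD 30, one-sided 2.5%: t-based power 0.8015 at 64) but has no bearing on BAP.

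**Step 1: adjusting for pre-treatment BAP.** Let s0 and s2 be the standard deviations at pre-treatment and week 24, and r02 their correlation.

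- Variance of the change score: s0² + s2² − 2·r02·s0·s2.
- Residual variance after ANCOVA on pre-treatment: s2²(1 − r02²).
- Difference: (s0 − r02·s2)², which is never negative.

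So ANCOVA never has the larger residual variance, whatever s0 and s2 are. The size of the gain does depend on them, and it vanishes if s0 = r02·s2.

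With equal variances, the ratio of ANCOVA to change-score variance is (1 − r02²) / [2(1 − r02)] = (1 + r02)/2.

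| Assumed r02 | Change score | ANCOVA | Ratio | Interval width |
|---|---|---|---|---|
| 0.5 | 1.00 | 0.75 | 75% | √0.75 = 0.866, about 13% narrower |
| 0.7 | 0.60 | 0.51 | 85% | √0.85 = 0.922, about 8% narrower |

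Variances are in units of the week-24 variance. The formulas are exact for absolute change or for change in log BAP. For raw percent change they are only a guide, because the pre-treatment value is also the denominator.

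**Step 2: adding week-8 BAP.** Let r12 be the week-8/week-24 correlation and r01 the pre-treatment/week-8 correlation. With equal variances the residual variance is 1 − R², where R² = (r12² + r02² − 2·r12·r02·r01)/(1 − r01²). Assumed ranges: r02 0.5–0.7, r12 0.6–0.8, r01 0.6–0.8.

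- Most favourable (r02 0.5, r12 0.8, r01 0.8): R² = (0.64 + 0.25 − 0.64)/0.36 = 0.694. Residual 0.306 against a change-score variance of 1.00, so 31%.
- Least favourable (0.7, 0.6, 0.8): R² = (0.36 + 0.49 − 0.672)/0.36 = 0.494. Residual 0.506 against 0.60, so 84%.
- All three at 0.7: R² = (0.49 + 0.49 − 0.686)/0.51 = 0.576. Residual 0.424 against 0.60, so 71%.

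The range of 31% to 84% is too wide to promise a figure. In the least favourable case week 8 adds almost nothing to pre-treatment adjustment alone (84% against 85%).

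**The case against.** **Against the precision point.** The t-test is a valid randomised comparison and contradicts nothing in the protocol. A statistical analysis plan exists ({20b} refers to one) and may specify adjustment. The size of the gain rests on correlations the documents do not give. All of this is true. It means the point is an improvement and not the correction of an error, and that its size is illustrative. It does not remove the point: {20a} names the unadjusted t-test as the method, so this is a comment on a stated choice, and the direction of the gain does not depend on the assumed correlations.

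**Against using week 8.** Randomisation takes place at registration ({16c}) and the trial is open-label ({17a}), so week-8 BAP is a post-randomisation value. Differences in adherence or withdrawal before day 57 could affect it. The article gives the sample's timing only as 8 weeks and does not place it before the switch. This objection stands, so week 8 belongs at most in a sensitivity analysis, with its timing stated.

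**A stronger reading.** A reader might infer that the test's week and scale are left open, so that a week-8 comparison, made on identical scheduled dosing and able to show no regimen effect, could be run as well. If both weeks were tested at 5% with both nulls true, the chance of at least one rejection would be 1 − 0.95² = 9.75% under independence, and about 9.1%, 8.4% and 7.0% at assumed correlations of 0.5, 0.7 and 0.9. The documents do not support that reading. {12} and the title of item (4) both fix percent change at 24 weeks, and the test sits under that title. Week 8 is given a summary and a graph, which is a legitimate use, and no between-arm week-8 test is planned. On the natural reading there is one test and the error rate is 5%.

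**Conclusion.** The point holds as a recommended improvement in method plus a minor clarification of wording.

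- The unadjusted t-test on change is valid but gives up precision. Adjusting for pre-treatment BAP would leave about 75% to 85% of the change-score variance, an interval about 8% to 13% narrower. This assumes equal variances and a pre-treatment/week-24 correlation of 0.5 to 0.7; the gain would be smaller at higher correlations, and different if the variances differ.
- Adding week-8 BAP might leave anything from 31% to 84% under the assumed ranges. That is conditional on the sample preceding the day-57 switch and on early adherence not differing by arm.
- The mention of amount and the missing week in the test and interval sentences are loose drafting against an endpoint fixed elsewhere. They do not amount to a plan for several tests.

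**What to change.** In item (4) of {20a}:

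1. Replace the t-test with an ANCOVA of week-24 BAP with arm and pre-treatment BAP as terms, two-sided 5%, reporting the adjusted difference with its 95% confidence interval. The outcome may be percent change, or log BAP back-transformed to a percent difference. Name one.
2. In the test and interval sentences write percent change at week 24 (or the log-scale equivalent, if chosen) and delete amount.
3. State that week 8 is summarised and graphed only, with no between-arm test.
4. Optionally, add week-8 BAP as a further covariate in a sensitivity analysis, and state that the sample is drawn before the day-57 switch.

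The cost is a few lines of text and no new data. The result becomes a covariate-adjusted difference and not a simple difference in mean changes, and a simple rule is needed for patients with a missing covariate value.
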